## **Introduction**

### **Background**

Chronic pain is characterized by changes in the central processing of sensory inputs. Quantitative sensory tests (QST) explore central excitability in humans and have the potential to detect altered central pain processing in individual patients [1].

QST were developed to assess the responses to sensory stimuli for research purposes, providing psychophysical and electrophysiological methods for the assessment of the nociceptive system [1, 2]. Reliability is an essential condition for using QST in research and clinical practice. It can be defined as the consistency of measurements across time, patients or observers, and the extent to which it is error-free [3]. Three categories have been assessed for reliability in QST measures: intra-rater, inter-rater and test-retest reliability [4] [5]. Reliability of QST measures in healthy volunteers are encouraging in regard to good repeatability of QST measures over the time in the same subjects. Inter-rater reliability, a prerequisite to compare different measures in between different studies, are also highly encouraging [6] [7] [8] [9] [10].

Under normal conditions, pain after application of a test nociceptive stimulus is attenuated by the application of an additional “conditioning” noxious stimulus to a remote body region, reflecting diffuse endogenous inhibition [11, 12]. This is defined as conditioned pain modulation (CPM), also known as the “pain inhibits pain” paradigm. CPM has been object of much work in the last years. It goes back to the exploration of endogenous analgesia via descending pain-modulatory systems, which started about three decades ago in animal models [13]. Descending inhibitory pathways are under cerebral control, mediating modulation of pain perception by emotional, motivational and cognitive factors [13, 14]. Alterations of CPM are a known risk factor concerning acute and chronic pain syndromes [15].

### **Aims**

The primary aim of the present study is to assess the reliability of CPM using the nociceptive withdrawal reflex as test stimulus and the ice water test as conditioning stimulus in 34 consecutive patients, with a 7 days interval between two sessions.

Secondary aim is to compare the reliability of CPM with the nociceptive withdrawal reflex to the reliability of CPM assessed with subjective pain assessments, i.e. pain threshold and pain intensity after electrical stimulation.

## **Methods**

### **Design**

Repeated assessments of CPM using the nociceptive withdrawal reflex threshold, electrical pain detection threshold and suprathreshold electrical stimulation of the skin, with ice-water as conditioning stimuli in all three models. There will be a 7 days interval between two measurements.

### **Setting**

Pain Division of the Department of Anesthesiology and Pain Therapy, University Hospital, Inselspital Bern, Switzerland.

### **Subjects**

We will test 34 consecutive pain-free volunteers. The volunteers will receive a compensation of 40 Swiss Francs for their participation.

#### **Inclusion criteria:**

- Male gender in order to eliminate cyclic hormonal variation.

#### **Exclusion criteria:**

- Age less than 18 or more than 65 years;
- Signs or suspicion of neurological disease or dysfunction;
- Ongoing treatment with any drug known to influence pain modulation: any analgesic, antidepressant, anticonvulsant or benzodiazepine;
- Intake of any analgesic drug during the 48h preceding the experiment.

#### **Selection and recruitment**

Subjects will be recruited in the Faculty of Medicine and the University Hospital of Bern with advertisement.

### **Pain tests**

#### **a- Mechanisms explored**

The primary outcome variable will be the reliability of CPM by ice water test and nociceptive withdrawal reflex. The additional measures will be secondary outcomes. They are the reliability of CPM using the ice water test as conditioning stimulus for all models, the pain detection threshold and the pain rating to cutaneous electrical stimulation as test stimuli.

#### **b- General methodological aspects**

During the experimental session, patients will be positioned in a comfortable supine position, with the upper body elevated by 30°, in a closed and quiet room. The tests will be performed on the dominant body side.

Training sessions of the pain tests will be performed before starting the experiment, until the subjects will be familiar with the testing procedures.

In all volunteers the second pain test session will be performed at the same time of the day ( $\pm 2$  hours in regard to the first experimental session), in order to rule out possible circadian influences on pain sensitivity.

#### **c- Electrical stimulation.**

Electrical stimulation will be performed through bipolar surface Ag/AgCl-electrodes placed just distal to the lateral malleolus (innervation area of the sural nerve). Electromyographic (EMG) reflex responses to electrical stimulation will be recorded from the middle of the biceps femoris and the rectus femoris muscles (Ag/AgCl-electrodes). Stimulation and EMG recordings will be made by a computer-controlled constant current stimulator (NCS System, Evidence 3102 evo, Neurosoft, Russia).

A 25 ms, train-of-five, 1 ms, square-wave impulse (perceived as a single stimulus), will be delivered. The current intensity will be increased from 1 mA in steps of 1 mA until: 1) a biceps femoris reflex with an amplitude exceeding 20  $\mu$ V for at least 10 ms in the 50-150 ms post-stimulation interval will be detected (single stimulus *reflex* threshold); and 2) a pain sensation will be evoked (single stimulus *pain* threshold). The single stimulus pain detection threshold will be multiplied by 1.5 to obtain a suprathreshold current intensity. Pain intensity after delivery of this suprathreshold stimulus will be assessed on the numerical rating scale (NRS), whereby 0=no pain and 10=worst pain imaginable.

#### **d- Ice water test**

The ice water test was used as conditioning stimulus. This test was chosen because it was shown to induce strong CPM in previous studies [19] [20].

The device consists of a container separated into an outer and an inner part by a mesh screen. The mesh screen prevents direct contact between the ice (placed in the outer part) and the hand of the subject (placed in the inner part). The water is regularly mixed to maintain the temperature in the inner part near to 0°C, as monitored by a thermometer with a digital display ( $\pm 0.1^\circ\text{C}$ ).

The subject places his hand, wide open and to the wrist, into the inner part of the container. He is asked to keep it in the water until he feels an intolerable sensation of pain and is forced to remove his hand from the container, in any case for a maximum time of 2 min.

#### **e- Conditioned pain modulation (CPM)**

As explained in the introduction, this method explores the endogenous modulation of nociceptive input. Under normal conditions, pain after application of a test nociceptive stimulus is attenuated by the application of an additional “conditioning” noxious stimulus to a remote body region, reflecting diffuse endogenous inhibition [11, 12].

In the present study, the threshold of the nociceptive withdrawal reflex measured at the biceps femoris and the ice water test applied at the hand are used as primary “test” and “conditioning”

stimuli, respectively. An increase in the nociceptive withdrawal reflex threshold immediately after ice water test is an indication of efficient CPM.

The nociceptive withdrawal reflex threshold is measured again at the same time as the subject is withdrawing the hand from the water (one single measurement). CPM is measured as the difference in the thresholds between measurements after and before the ice water test.

The cutaneous electrical pain detection thresholds (secondary outcome) will be assessed at the same time as the threshold for the nociceptive withdrawal reflex. For the pain rating at suprathreshold stimulation (additional secondary outcome), the procedure with the ice water test will be repeated 30 min after the first recordings. This will be done in order to avoid a possible influence of the reflex measurement on a subsequent assessment of pain intensity.

### **Sample size considerations**

The sample size calculation is based on two parameters: The detection of CPM and the reliability of the nociceptive withdrawal reflex.

#### **a. Detection of CPM**

CPM is measured as the difference in the stimulation threshold of the nociceptive withdrawal reflex between measurement after and before the ice water test. In a previous study, the nociceptive withdrawal reflex after single stimulation had a mean of 17 mA, a SD of 4 mA, and a range of 5-31 mA [21]. In order to detect a minimal difference of 2.0 mA between nociceptive withdrawal reflex threshold after and before ice water stimulation, with an expected SD of change of 4.0 mA, a probability of 80% that the study detects a difference at a two-sided significance level of 0.05, a paired t-test analysis yields a total of 34 patients.

#### **b. Reliability**

The sample size for a test-retest reliability study depends on the minimally acceptable level of reliability  $\rho_0$ , the target level of reliability  $\rho$  (measured as intraclass correlation coefficient), and the number of repetitions of the measurement  $n$ . The values for type I and type II errors ( $\alpha$  and  $\beta$ ) are set to 0.05 and 0.20, respectively [22]. Considering a minimum number of measurements of  $n = 2$  (one measurement per session and two different sessions), reliability values of  $\rho_0 = 0.5$  as the minimally accepted reliability and  $\rho = 0.8$  as the expected reliability [10] [23], the minimum sample size for this experiment is 22 subjects.

In summary, 34 subjects are required in order to detect CPM and estimate test-retest reliability.

### **Statistical Analysis**

The between-session reliability (also referred to as *stability over time*) of the nociceptive withdrawal reflex to single electrical stimulation will be assessed using multiple methods described below.

- *Intraclass correlation coefficient (ICC)*: it measures the relative homogeneity within sessions in relation to the total observed variation between sessions. For this analysis, a two-way mixed model using absolute agreement will be selected, and ICC for single measurements will be reported. ICC values above 0.75 are indicative of good reliability [24]. An  $F$  test with a hypothesized ICC value of 0.5

(representing a fair reliability level) will also be carried out in order to determine if the ICC values obtained are significantly different from this level.

- *Coefficient of variation (CV)*: it represents the standard error of measurement expressed as a percentage of the subject's average threshold. The CV can be interpreted as the percentage of deviation from the average threshold below which 68% of the differences between sessions may be expected to lie [25].

- *Bland-Altman agreement analysis*: it is based on the analysis of the average vs. the difference of the thresholds between two given sessions, from which the so called *limits of agreement (LA)* can be derived, as the average difference  $\pm 1.96$  times the standard deviation of the differences. The LA delimit the range within which 95% of the differences between thresholds in two single sessions may be expected to lie. In close relation to this definition, the *coefficient of repeatability (CR)* is defined as the value below which 95% of the *absolute* differences between thresholds in two single sessions may be expected to lie. If there is no systematic bias in the thresholds between sessions, the average difference between thresholds is expected to be zero, and the LA and the CR should be similar [26].

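### The primary outcome is the reliability of CPM (the after-minus-before change), but the Statistical Analysis and the reliability sample size address the reflex threshold itself

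*Protocol*

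**What the plan says.** **Target.** The primary aim (Protocol, Aims) is "to assess the reliability of CPM using the nociceptive withdrawal reflex as test stimulus", with ice water as conditioning stimulus. Under Pain tests, a- Mechanisms explored: "The primary outcome variable will be the reliability of CPM by ice water test and nociceptive withdrawal reflex". Section e- Conditioned pain modulation (CPM) makes this operational: "CPM is measured as the difference in the thresholds between measurements after and before the ice water test". Sample size considerations, a. Detection of CPM, repeats that definition.

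**Analysis.** The Statistical Analysis section announces the between-session reliability "of the nociceptive withdrawal reflex to single electrical stimulation will be assessed using multiple methods described below". It then lists three methods:

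- a single-measurement, absolute-agreement ICC, with an F "test with a hypothesized ICC value of 0.5";
- a CV, read as the "percentage of deviation from the average threshold below which 68% of the differences between sessions may be expected to lie";
- a Bland-Altman analysis, based on the "analysis of the average vs. the difference of the thresholds between two given sessions", with limits of agreement and a coefficient of repeatability also defined on thresholds.

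The section mentions neither CPM, the change score nor the ice water test.

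**Sample size.** The opening of Sample size considerations names two separate parameters: detecting CPM, and the reliability of the reflex. Section b. Reliability sets 0.5 as the minimum and 0.8 as the expected ICC, with one measurement in each of two sessions, and arrives at 22 subjects. The total of 34 comes from the CPM detection calculation.

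**The concern.** The reflex threshold and the change in that threshold are different variables, and their reliabilities can differ widely. A threshold ICC is high when people differ stably in their thresholds. Those stable differences are present before and after immersion, so they cancel when one is subtracted from the other. What remains is the person's CPM effect plus the measurement error of two readings instead of one.

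If the section is followed as written, the study will estimate and test how reproducible the reflex threshold is. Its primary question, whether CPM is reproducible, will go unanswered. That question is open on the protocol's own account: the Introduction reports very poor CPM reliability in the group's earlier data from patients with low back pain.

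**Working it through.** **1. The planned sizes reproduce, so this is not an arithmetic error.**

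- CPM detection (difference 2.0 mA, SD of change 4.0 mA, two-sided 0.05, 80% power): the paired t-test with the noncentral t distribution gives 34 subjects, power 0.808.
- Reliability: k = 1 + 2(z_α + z_β)² n / [(ln C)² (n − 1)], with C = (1 + nθ₀)/(1 + nθ) and θ = ρ/(1 − ρ). For ρ₀ = 0.5, ρ = 0.8 and n = 2: θ₀ = 1, θ = 4, C = 3/9. With one-sided α = 0.05, k = 21.49, so 22 as stated. The protocol does not give the sidedness; a two-sided α gives 27.01, so 28.

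**2. What a threshold ICC of 0.8 implies for CPM.** Inputs: threshold SD 4 mA and SD of change 4.0 mA (section a. Detection of CPM); threshold ICC 0.8 (section b. Reliability). Assumptions added here: the same SD and the same ICC before and after immersion, and measurement errors that are independent of each other.

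- Pre-post correlation within a session: r = 1 − SD_change²/(2 SD²) = 1 − 16/32 = 0.5.
- Reliability of the difference: (0.8 − r)/(1 − r) = 0.3/0.5 = 0.60. A simulation under the same model also gives 0.600.
- Check by variances: the error variance of one threshold is 0.2 × 16 = 3.2. The change carries 2 × 3.2 = 6.4 out of a total of 16, so the ICC is 1 − 6.4/16 = 0.60.

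**3. What the test against 0.5 does with 34 subjects.** With two sessions and no systematic shift between them, power = P(F > F_crit × q) on 33 and 33 degrees of freedom, where q = [(1 + 0.5)/(1 − 0.5)] / [(1 + ρ)/(1 − ρ)]. The one-sided 5% critical value is 1.788.

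- Threshold, ρ = 0.8: q = 3/9, power about 93% (about 87% two-sided).
- CPM, ρ = 0.60: q = 3/4, power about 20%. The formula in step 1 would ask for 300 subjects (299.8).

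**4. Range over the pre-post correlation**, threshold ICC held at 0.8:

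| Pre-post correlation | Implied SD of change, √(32(1 − r)), mA | CPM ICC | N from step 1 formula | Power with 34 (one-sided) |
|---|---|---|---|---|
| 0.3 | 4.73 | 0.71 | 53 | about 63% |
| 0.4 | 4.38 | 0.67 | 96 | about 42% |
| 0.5 | 4.00 | 0.60 | 300 | about 20% |
| 0.6 | 3.58 | 0.50 | not attainable | 5% |

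Only the row with r = 0.5 matches the stated SD of change.

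**5. Errors shared within a session.** If the before and after errors correlate at c, the error variance of the change falls to 6.4(1 − c). Holding the SD of change at 4.0 mA, the CPM ICC is 1 − 0.4(1 − c): 0.60 at c = 0, 0.70 at c = 0.25 and 0.80 at c = 0.5. At 0.80 the planned 22 would stand for CPM too. The protocol gives no value for c.

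**6. The CV does not carry over to CPM.** SEM/mean is 4√0.2/17 = 10.5% for the threshold (mean 17 mA) but 4√0.4/2 = 126% for CPM at ICC 0.60 and a mean of 2 mA. If CPM were normal with mean 2 and SD 4, about 31% of values would be negative.

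**The case against.** The best defence is that the wording is shorthand. Aims, outcomes, the CPM section and Relevance all make CPM the target, the method descriptions read as generic definitions, and the ICC item does not itself mention thresholds. But the ICC item takes its variable from the section's opening sentence, which names the reflex. The CV and Bland-Altman items name thresholds. The sample size section lists the detection of CPM and the reliability of the reflex as two separate things, and the two sources cited for the reliability values have titles about the reflex threshold. The shorthand reading does not survive that.

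Several stronger readings are tempting, and the documents do not support them.

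- *The threshold test would pass whatever the true reliability of CPM.* This holds only for the pre-immersion threshold with independent errors. The protocol measures the threshold before and after immersion and does not say which one is analysed; a post-immersion threshold contains the CPM effect and would respond to its instability.
- *CPM could be pure noise under the planning values.* A CPM ICC of 0 with independent errors implies an SD of change of √6.4 = 2.53 mA, not the stated 4.0 mA. It is an illustration, not a planning scenario.
- *The investigators would present a threshold ICC as a CPM ICC.* Nothing says so. The fault is that the primary outcome has no matching analysis.
- *The two secondary CPM measures lack an analysis.* Such methods may stand in a SAP that is not at hand, so this is not part of the point.

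**Conclusion.** The point holds as a contradiction within the protocol. The primary outcome is the reliability of a change score; the written analysis and the reliability sample size concern the threshold from which that change is computed. The contradiction rests on the text alone and needs no modelling assumption. It is not a detail left to a SAP, because the protocol fixes the ICC form, the null value and the agreement limits, and fixes them on another variable.

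The size does need assumptions. With equal SDs before and after, a threshold ICC of 0.8 at both times and independent errors, the planning values give a CPM ICC of about 0.60 and power of about 20%, against about 93% for the pre-immersion threshold. Over pre-post correlations of 0.3 to 0.6 the CPM ICC runs from 0.71 to 0.50 and power from about 63% to 5%; within-session shared error would raise both. A reader might infer that the trial must enrol about 300 subjects. That does not follow: 34 still serves CPM detection, and the CPM ICC can be reported with the precision that 34 gives.

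**What to change.** 1. **Statistical Analysis.** State that the single-measurement absolute-agreement ICC, the F test against 0.5, and the Bland-Altman limits of agreement and coefficient of repeatability are computed on CPM (threshold after minus threshold before) per subject, session 1 against session 2.
2. **Supporting analysis.** Keep the reliability of the raw pre-immersion threshold, labelled separately as such.
3. **CV.** Use it for the raw threshold only. The change score has an expected mean of about 2 mA and can be negative, so a CV on it would be unstable.
4. **Sample size considerations.** State that the expected ICC of 0.8 and the 22 subjects refer to the reflex threshold. Then either justify 0.8 for CPM or restate the power or precision that 34 subjects give for the CPM ICC.

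The cost is wording in two sections, with no new subjects, data or procedures. The downside is that the reported ICC and the stated power will probably look less favourable.

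### The CV is interpreted as the 68% limit for between-session differences, but as defined it covers about 52% of them; the interpretation needs correcting, the CV itself does not

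*Protocol*

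**What the plan says.** The protocol's Statistical Analysis section lists three methods for between-session reliability: the intraclass correlation coefficient (ICC), the CV and a Bland-Altman analysis.

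- **CV, definition:** "it represents the standard error of measurement expressed as a percentage of the subject's average threshold".
- **CV, interpretation, in the next sentence:** "the percentage of deviation from the average threshold below which 68% of the differences between sessions may be expected to lie".
- **Bland-Altman:** the limits of agreement (LA) are the mean difference plus or minus 1.96 "times the standard deviation of the differences". The coefficient of repeatability (CR) is the value below which "95% of the *absolute* differences between thresholds in two single sessions may be expected to lie".

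The reliability part of the sample size section fixes the layout of the data: "one measurement per session and two different sessions".

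**The concern.** The two CV statements are on different scales. The definition concerns the error in one measurement. The interpretation concerns the difference between two measurements, each with its own error. A difference is more variable than either of its parts, so one SEM cannot be the 68% limit for both.

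What is at stake is how the CV is read. Reliability is the primary outcome, and the CV is one of the three measures listed for it. Someone who takes the interpretation literally would set the typical session-to-session change at 1/√2 = 0.71 of its actual size, about 29% too small, which flatters the measure. The Relevance section looks ahead to clinical use and to detecting disturbances in individuals. There, the scale of between-session differences decides whether a change in one person exceeds measurement noise.

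**Working it through.** **Inputs**

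- CV = SEM / subject's average threshold (Statistical Analysis, CV).
- Stated coverage: 68% of between-session differences (same place).
- One measurement in each of two sessions (Sample size considerations, b. Reliability).
- For illustration only: reflex threshold mean 17 mA and SD 4 mA (Sample size considerations, a. Detection of CPM); ICC 0.5 as the minimum accepted and 0.8 as expected (b. Reliability).

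**Model (assumed)**

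X₁ = T + e₁ and X₂ = T + e₂, where T is the subject's true average. The errors are independent and normal with SD equal to the SEM in both sessions, and there is no systematic shift between sessions.

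**Step 1. Where 68% comes from.** For one measurement around the subject's true average:

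P(|X − T| < SEM) = 2Φ(1) − 1 = 0.683.

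This reproduces the protocol's figure, but the quantity is not a difference between sessions.

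**Step 2. Coverage of between-session differences.** D = X₂ − X₁ = e₂ − e₁, so SD(D) = √(SEM² + SEM²) = √2 × SEM. Then:

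P(|D| < SEM) = 2Φ(1/√2) − 1 = 2Φ(0.707) − 1 = 0.5205.

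Dividing both sides by the subject's average leaves this unchanged, so it holds for the CV as a percentage. A simulation of 1,000,000 subjects gave 0.521 at ICC 0.5 and at ICC 0.8.

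**Step 3. The limit that does cover 68%.** One SD of D gives 2Φ(1) − 1 = 0.683, so the limit is √2 × SEM = 1.414 × CV.

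**Step 4. Other readings**

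| Reading | Coverage of one SEM |
|---|---|
| Absolute difference between sessions | 52.0% |
| Signed difference, one-sided, Φ(0.707) | 76.0% |
| One measurement against the observed two-session mean, 2Φ(√2) − 1 | 84.3% |
| One measurement against the true average | 68.3% |

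Neither reading as a between-session difference gives 68%.

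**Step 5. Systematic shift.** With a shift expressed in units of the error SD, coverage is 49.4% for a shift of 0.5 SEM and 42.1% for a shift of 1 SEM.

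**Step 6. Scale of the LA and CR.** Without a shift, CR = 1.96 × SD(D) = 1.96 × √2 × SEM = 2.77 × SEM. The matching 68% limit is CR/1.96 = 1.414 × SEM, as in step 3.

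**Step 7. Illustration, raw reflex threshold, assuming SEM = SD × √(1 − ICC)**

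| ICC | SEM | CV (SEM/17) | √2 × SEM | 68% limit (√2 × SEM/17) |
|---|---|---|---|---|
| 0.8 | 4 × √0.2 = 1.79 mA | 10.5% | 2.53 mA | 14.9% |
| 0.5 | 4 × √0.5 = 2.83 mA | 16.6% | 4.00 mA | 23.5% |

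At ICC 0.8, scaling the CV as if it were the SD of the differences would suggest a 95% range of ±1.96 × 1.79 = ±3.5 mA. The protocol's own LA half-width would be 1.96 × 2.53 = 5.0 mA.

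**The case against.** The strongest reply is that this is a slip in an explanatory sentence and not a fault in the analysis. The definition of the CV is sound. The sentence also speaks of deviation from the average threshold, and for one measurement around the true average 68% is correct. No acceptance limit, test or decision is tied to the CV: the 0.75 benchmark and the test against 0.5 both concern the ICC, and the sample size does not use the CV. The LA and CR give the bound on session-to-session change on the right scale, from the same data.

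All of this stands, and it limits the reach of the point. It does not rescue the sentence, which applies its 68% to differences between sessions.

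It can also be said that the sentence, unlike the CR definition, does not specify absolute differences. Read one-sided, coverage is 76%, which is still not 68%.

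A reader might infer that the computed CV contradicts the LA and CR. It does not: without a shift, CR = 2.77 × SEM is fully consistent with CV = SEM/average, and only the verbal 68% is out of scale. A reader might also infer that the study will publish the measure as more stable than it is. The protocol does not say how the CV will be presented, so that is conjecture.

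**Conclusion.** The stated interpretation of the CV is wrong. As defined, one CV covers about 52% of absolute between-session differences, and the 68% limit is 1.41 × CV. This rests on normal errors, equal error variance in the two sessions and no systematic shift; a shift lowers the coverage further.

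The error is confined to interpretation. The computed CV, ICC, LA, CR and sample size stand as they are. The percentages in step 7 combine an SD from a previous study with planning values for the ICC. They describe the raw reflex threshold, and it would be a mistake to read them as the size of the error for conditioned pain modulation, the primary outcome, which is a difference between two thresholds.

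The point still merits correction, because it is a definite coverage statement about one of the three listed reliability measures and it errs in the direction that makes the measure look more stable.

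**What to change.** Choose one of two corrections to the CV paragraph in Statistical Analysis:

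1. Keep the CV as defined and restate its meaning: about 68% of single measurements are expected within one CV of the subject's true average. This costs one sentence, and no reported figure changes.
2. If a 68% limit for between-session differences is wanted, report √2 × CV and label it so. This costs one multiplication; that figure is 41% larger than the CV, which itself stays the same.

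Under the second option, check the result against the SD of the differences used for the LA and CR. Expressed in mA, the two should agree when there is no session shift. In either case, state the assumptions of normal errors and no systematic shift next to the 68%.
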